**Methods:**

We will conduct a clinical, controlled, randomized, double-blind trial that will include sedentary men and women who are 21–60 years old and who have diagnosed systolic HF and a left ventricular ejection fraction of less than 45%. Participants will be randomly assigned to one of two groups: experimental and control. The control group will follow the conventional CR protocol, and the experimental group will follow the conventional CR protocol associated with IMT 7 days a week. The two proposed exercise protocols will have a frequency of three times a week for a period of 12 weeks. The sympathetic innervation of the cardiac muscle, the maximum and submaximal functional capacity, diaphragm mobility and thickness, and the quality of life of the participants will be evaluated before and after the intervention protocol.

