### Criteria for discontinuing or modifying the allocation

The criteria for discontinuing or modifying the allocation are worsening of symptoms, clinical instability, change in the class of medications, and emergence of serious infectious or viral diseases (or both) which are difficult to control.

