### Evaluated outcomes

The participating individuals will be evaluated on the first day of evaluation by collecting their clinical history, applying the quality-of-life questionnaire, and reading the echocardiogram. Then they will be submitted to an anthropometric evaluation (height and weight through a digital scale with anthropometer [model W300, Welmy, São Paulo, Brazil] with a capacity of 300 kg, precision of 50 g, and an anthropometer with limit of 2 m and body mass index by dividing body weight by height squared), evaluation of vital signs through a multiparameter monitor (2023, Dixtal, Manaus, Brazil), evaluation of pulmonary function through spirometry, and evaluation of respiratory muscle strength through manovacuometry. Ultrasonography will be performed on the second day to measure the diaphragm muscle thickness and mobility (secondary outcome endpoint), and maximum functional capacity (primary outcome) will be evaluated by a responsible medical professional.

The Glittre-ADL test will be performed on the third day for submaximal measurement of functional capacity (secondary outcome). Finally, the patients will be referred to a specialized hospital on the fourth day for myocardial scintigraphy (primary outcome). After all the evaluation procedures have been carried out and recorded on the corresponding file, the participants who are already randomly allocated will start their respective IMT protocols associated with CR; then the subjects will be submitted to the same evaluation process at the end of 36 sessions, along with a question that measures the degree of satisfaction with the treatment. Figure 2 and the checklist provide an overview of standardized items for clinical trials according to Standard protocol items: Recommendations for interventional trials (SPIRIT) [15].

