### Randomization, allocation, and blinding

The subjects will be randomly assigned to groups through the website www.randomization.com in regard to the following protocols: control group (CR and “Sham” IMT) and experimental group (CR and IMT at 30% MIP). Then the allocation will be performed through numbered opaque envelopes by the researcher responsible for the weekly adjustment of the Powerbreathe load and they will only open the envelope corresponding to the patient at the time of the first adjustment. The entire randomization and allocation process will be carried out exclusively by the collaborating researcher, and the researcher will remain confidential until the end of the study. No other researcher or patients will be aware of which group they belong to, including the same one.

All of the patients will receive the training device and will have inspiratory muscle strength re-evaluated weekly to ensure patient masking, not being aware of whether the load is being increased or not. The device contains a protective cover that makes it impossible to visualize the imposed load. In addition, if the patient reports that the training is light, the researcher will tell them that it is natural and occurs as a result of training progression and improvement in muscle strength.

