#### Ergospirometry

The symptom-limiting cardiopulmonary exercise test (CPET), considered the gold standard in the evaluation of functional capacity, will be performed for all patients in the study, using a ramp protocol [18] on a treadmill (Centurium 300, Micromed, Brasília, Brazil) through the ErgoPC Elite® software program associated with electrocardiogram (Micromed) with 12 channels. The respiratory variables will be evaluated by a gas analyzer (Metalyzer II, Cortex, Leipzig, Germany) obtained under standard conditions of temperature, pressure and dry (StPD), breath-by-breath, and the patient will be breathing in a non-leaking facial mask during exercise. Pressure, gas, and volume calibration of the equipment will be performed before each test. Examinations will be considered only where patients have a respiratory exchange ratio of at least 1.1 in order to ensure that patients achieve maximal effort during the examination. The test will be performed by an experienced cardiologist in an environment equipped with all emergency equipment and trained personnel. The test time is the time required to acquire a maximum stress test while maintaining patient safety since all vital signs and the electrocardiogram signal will be continually evaluated.

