### Statistical methods

Descriptive statistics will be used, and the continuous variables will be presented as means or medians, standard deviations, and 95% confidence intervals. Categorical variables will be expressed percentages and absolute numbers. The normality of the data will be evaluated through the Shapiro–Wilk or Kolmogorov–Smirnov tests. The Levene test will be used to test the variance homogeneity.

The paired *t* test will be used for normal data or the Wilcoxon test for non-normal data to compare the pre and post intervention of adrenergic tone, maximum and submaximal functional capacity, and diaphragm mobility and thickness. The unpaired *t* test or Mann–Whitney test will be used in the comparison between the groups depending on the normality of the data, and the significance level will be accepted at a *P* value of less than 0.05. The effect size will be calculated by using Cohen’s d, and the results will be interpreted on the basis of Cohen as follows: small (0.21–0.49), medium (0.50–0.79), or large (≥0.80) [23]. All participants included in the initial assessment will be considered under the intention-to-treat according to the method of last observation carried forward. The statistical analysis will be carried out with the Statistical Package for the Social Sciences, version 22.0 (SPSS Inc., Chicago, IL, USA).

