However, in order to minimize any such effects, individuals will perform evaluation activities only when they are clinically stable. A suitable cardiologist for the ergospirometric test will be present and participate in the cardiopulmonary evaluation of all those involved. In addition, all professionals present will be able to attend emergency services for any possible intercurrences since they are all professionals with training in the health area and have knowledge in first aid, basic life support, and cardiopulmonary resuscitation. Moreover, there will be equipment and resources for pre-hospital care (oxygen cylinders, manual defibrillator, basic medical support supplies, and related drugs) in the laboratory in which the evaluations will be carried out, and it is also located close to one hospital which is an appropriate place for more complex approaches and which promises to receive patients in their emergency care unit in case of any adverse events. IMT does not present any risk for the patients who use it; proof of this is that it can be performed by the patient at home and without the need for supervision.

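### With a single post-training assessment, last observation carried forward is baseline carried forward, so every missing outcome is scored as exactly zero change

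*Protocol article*

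**What the plan says.** The Statistical methods section gives one rule for incomplete data: "All participants included in the initial assessment will be considered under the intention-to-treat according to the method of last observation carried forward". It states no other method and no sensitivity analysis.

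The visit structure appears in three places. The abstract says that the outcomes "will be evaluated before and after the intervention protocol". Evaluated outcomes describes the baseline work-up over four days and continues: "then the subjects will be submitted to the same evaluation process at the end of 36 sessions". Statistical methods uses paired tests "to compare the pre and post intervention of adrenergic tone, maximum and submaximal functional capacity, and diaphragm mobility and thickness" and unpaired tests between groups. The text describes no interim scintigraphy, exercise test, Glittre-ADL test, diaphragm ultrasound or quality-of-life assessment. Patients "will have inspiratory muscle strength re-evaluated weekly to ensure patient masking", but maximal inspiratory pressure (MIP) is not a named primary or secondary outcome.

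Three further statements bear on who will lack a second value:
- On stopping: "The criteria for discontinuing or modifying the allocation are worsening of symptoms, clinical instability, change in the class of medications", followed by serious infection.
- Under Ethical aspects: "individuals will perform evaluation activities only when they are clinically stable".
- Under Ergospirometry, for a primary outcome: "Examinations will be considered only where patients have a respiratory exchange ratio of at least 1.1".

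**The concern.** LOCF presupposes a series of measurements. With one measurement on each side of the intervention, the last observation of anyone without the second value is the baseline, and the imputed change is zero whatever happened to the patient.

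This is wrong in two opposite directions. Both arms receive a 12-week rehabilitation programme intended to improve function, so zero is too low for a patient lost for reasons unrelated to health. For a patient who deteriorated and was not re-evaluated, zero is too high. The method therefore cannot be defended as conservative: the direction of its bias depends on why patients are lost and how losses divide between the arms.

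The imputed zeros are then analysed as if measured, in both the within-group and the between-group tests. The rule covers both primary outcomes.

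**Working it through.** **1. The structural step.** The protocol states no sample size, effect, standard deviation or loss by arm, so there is no figure to reproduce. For visits {baseline, post}, a missing post value Y₁ is replaced by Y₀, so the imputed change is Y₀ − Y₀ = 0. This needs no assumption.

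**2. Form of the bias.** Let a share L of an arm be missing, and let the change of patients in that arm have mean m and SD s, with loss unrelated to outcome. Under LOCF the change is a mixture of 0 and the true distribution:
- mean = (1 − L)m
- variance = (1 − L)(s² + m²) − [(1 − L)m]²

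With equal L the between-group difference d becomes (1 − L)d: 90% of its value at L = 10%, 83% at 16.7%, 80% at 20%. With unequal loss and no true difference, the spurious difference is m times the difference in loss, against the arm that loses more.

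**3. Illustrative inputs (assumptions, not in the protocol).** Peak oxygen uptake, s = 2.5 mL/kg/min, rehabilitation gain 2 in controls, IMT effect 1.25 (0.5 SD), two-sided 5%, unpaired t test on change. For 80% power this needs 64 per arm. The plan's 20% increase gives 64 × 1.2 = 76.8, so 77. That inflation covers a loss of 1 − 1/1.2 = 16.7%, not 20%.

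**4. Equal loss, 77 per arm, L = 16.7%.**
- Difference: 0.833 × 1.25 = 1.04.
- Variances: control (m = 2) 0.833 × 10.25 − 1.667² = 5.76; experimental (m = 3.25) 0.833 × 16.81 − 2.708² = 6.68.
- LOCF: SE = √[(5.76 + 6.68)/77] = 0.402; 1.04/0.402 = 2.59; power Φ(2.59 − 1.96) ≈ 74%.
- Observed cases (64.2 per arm): SE = 2.5 × √(2/64.2) = 0.441; 1.25/0.441 = 2.83; power Φ(0.87) ≈ 81%, or about 80% with the t distribution.

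The LOCF standard error is the smaller of the two although it adds no information, and power still falls because the effect shrinks more.

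**5. Unequal loss, no IMT effect, 64 per arm, gain 2.** Variances are 5.985 at L = 10%, 5.64 at 20% and 5.215 at 30%.

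| Loss by arm | Spurious difference | SE | Ratio | Type I error |
|---|---|---|---|---|
| 10% vs 20% | 2 × 0.10 = 0.20 | √(11.625/64) = 0.426 | 0.47 | about 8% |
| 10% vs 30% | 2 × 0.20 = 0.40 | √(11.200/64) = 0.418 | 0.96 | about 16% |

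An observed-case analysis stays at 5% in both rows, because loss here is unrelated to outcome. At 30 per arm the LOCF figures are about 6% and 10%.

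**6. Hidden decline.** Suppose 15% of one arm and 5% of the other stop with a true change of −0.5 SD and are not re-evaluated. Their contribution to the difference should be −0.5 × 0.15 + 0.5 × 0.05 = −0.05 SD. LOCF sets it to zero.

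**The case against.** Several stronger readings are tempting, and the protocol does not support them.

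- **That every patient stopped for worsening is scored as unchanged.** The stopping section concerns discontinuing or modifying the allocation, not leaving follow-up. Nothing says that stopped patients skip the post assessment, and anyone who is evaluated is not imputed. The stability condition under Ethical aspects makes a missing value likely only while a patient remains unstable.
- **That some assessed patients would have no arm.** The envelope is opened at the first load adjustment, but Evaluated outcomes describes participants who complete the evaluations as allocated by then. An assigned but concealed arm is a natural reading. At most, the timing is ambiguous.
- **That false positives of 16% or more are to be expected.** That needs 10% versus 30% loss, and nothing in the protocol suggests such an imbalance: both arms receive the same rehabilitation and a masked device. At 15% versus 20% the error is about 5%. The figures also assume a test on change. The protocol does not say whether the unpaired test uses change or post values. With post values and an assumed baseline SD of 3 to 5, the 16% falls to 7–9%.
- **That a model-based analysis by itself cures the problem.** A mixed model or multiple imputation assumes missing at random. Unless the covariates capture the decline, it credits a worsened patient with roughly the gain of similar completers, which is more favourable than zero.

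These objections limit the size and shape the remedy. They do not touch the zero-change imputation, which follows from the stated visits and the stated rule. Nor is this detail that can be left to an unseen analysis plan: the protocol itself names the method.

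**Conclusion.** The concern holds. For every named outcome the stated rule is baseline carried forward: exactly zero change for any patient without a post value, shrinkage to (1 − L) under equal loss, a spurious difference under unequal loss, and standard errors that are too small. The shrinkage and spurious-difference formulae assume that loss is unrelated to outcome. Where worsened patients are not evaluated, their decline is also hidden.

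The size is moderate in plausible cases: about six points of power under the plan's own inflation, and type I error near 8% for a ten-point imbalance in loss at 64 per arm. All such figures rest on the assumed SD, gain, effect and loss rates and on a change-score test. The structural point does not. Figures 1 and 2 were not available, but the text describes no interim outcome visit.

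**What to change.** Amend Statistical methods as follows:

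1. Replace LOCF as the primary method with a likelihood-based baseline/post model, or with multiple imputation by arm using the baseline outcomes and the weekly MIP.
2. Define the intention-to-treat set as all randomised patients, analysed in the arm assigned.
3. State that patients who stop the intervention are still invited to the planned post assessment whenever it can be done under the protocol's own stability condition.
4. Prespecify a delta-adjusted sensitivity analysis for patients stopped for worsening who have no post value. This is an essential part of the change, because the new primary analysis may credit them with completers' gains.
5. Keep LOCF only as a labelled sensitivity analysis.

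The cost is revised wording, modest extra analysis work, some return visits for stopped patients, and somewhat wider intervals. The change should be made before unblinding.

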### Study design

This is a clinical, controlled, randomized, double-blind, and feasible trial developed in partnership with the Department of Physical Therapy of the Federal University of Pernambuco (*Universidade Federal de Pernambuco*) and *Hospital das Clínicas* of Pernambuco, and the patients come from the main reference centers of Recife-Brazil for the care of patients with HF. Figure 1 represents the follow-up flowchart of the study according to the CONSORT (Consolidated Standards of Reporting Trials) [12]. The sample will be calculated from the result of the first 20 patients through the GPower 3.1 software program [13] with α of 0.05 and a power of 80%. It will be calculated for all study variables, and the largest number will be increased by 20% to compensate for possible follow-up losses.

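### With one baseline and one final measurement of each named outcome, last observation carried forward scores a participant without a usable final value as exactly zero change

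*Protocol article*

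**What the plan says.** **Missing data.** Protocol article, Statistical methods: "All participants included in the initial assessment will be considered under the intention-to-treat according to the method of last observation carried forward". No other rule for missing outcomes is stated.

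**Schedule.** The abstract's Methods paragraph closes its list of outcomes with "the quality of life of the participants will be evaluated before and after the intervention protocol". Evaluated outcomes describes four baseline days and then one repeat: "the subjects will be submitted to the same evaluation process at the end of 36 sessions". The paired comparisons in Statistical methods are pre versus post only. The one measure described as repeated during treatment is in Randomization, allocation, and blinding, where patients "will have inspiratory muscle strength re-evaluated weekly to ensure patient masking". Inspiratory strength is not a named primary or secondary outcome.

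**Ways to lose a final value.**
- The section on discontinuation states: "The criteria for discontinuing or modifying the allocation are worsening of symptoms, clinical instability, change in the class of medications", together with serious infection.
- Ethical aspects: "individuals will perform evaluation activities only when they are clinically stable".
- Ergospirometry: "Examinations will be considered only where patients have a respiratory exchange ratio of at least 1.1".
- Study design expects losses: "the largest number will be increased by 20% to compensate for possible follow-up losses".

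**The concern.** Carrying an observation forward presupposes something observed after treatment began. Here nothing is, for any named outcome. The carried value is the baseline, and the imputed change is zero by construction.

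That is a fixed guess, and the stopping criteria make it a poor one. Patients are stopped largely because they deteriorate. The final assessment is tied to a session count that a stopped patient does not reach, and unstable patients are not evaluated. Patients who got worse may therefore be recorded as unchanged. A final exercise test rejected for a low exchange ratio and not repeated takes the same route, in a primary outcome.

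Three things are at stake: a spurious difference between arms if stopping is unequal, a diluted estimate if stopped patients keep some benefit, and the accuracy of the intention-to-treat label.

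**Working it through.** The plan states no figure to reproduce: the sample size is to come from the first 20 patients, and no effect size, SD or stopping rate is given. The structural point needs no arithmetic. With one pre and one post value, a missing post value becomes the pre value, so change = 0. What follows only illustrates size.

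**Assumptions (not in the article).** Change has SD 1 and higher is better. μ is the average improvement, equal in both arms when there is no true effect. p is the share stopped, nobody is reassessed, and r is the correlation between stopping and outcome, from 0.3 (mild) to 1 (worst responders always stopped). The 32 per arm is 26 (0.8 SD effect, 80% power) × 1.2 = 31.2, rounded up.

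**Step 1: no true effect.** The arm mean under carry-forward is μ(1−p) + r·φ(z_p), where φ is the normal density and z_p the normal quantile of p. Let arm A be the arm stopped less often and B the other. The bias in A − B is

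μ(p_B − p_A) + r[φ(z_A) − φ(z_B)].

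With equal stopping both terms cancel: bias 0, simulated type I error about 5%.

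With p_A = 0.10 and p_B = 0.30, φ = 0.1755 and 0.3477, so the bias is 0.20μ − 0.172r:

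| μ | r = 0.3 | r = 0.7 | r = 1 |
|---|---|---|---|
| 0 | −0.05 | −0.12 | −0.17 |
| 0.3 | +0.01 | −0.06 | −0.11 |
| 0.5 | +0.05 | −0.02 | −0.07 |
| 0.8 | +0.11 | +0.04 | −0.01 |

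A negative value counts against the arm stopped less often. Simulated type I error at μ = 0 and 32 per arm (40,000 replicates, two-sided t test at 0.05) is about 5.7%, 9.1% and 15.6% for r = 0.3, 0.7 and 1.

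At 15%/25% stopping and μ = 0, the bias is −0.06 (r = 0.7) and −0.08 (r = 1). Reassessing half of the stopped patients at 10%/30% and μ = 0 roughly halves the bias, to −0.06 and −0.09, with type I error 5.6% and 6.8%.

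**Step 2: a true effect d, 20% stopped in each arm.** The selection terms cancel, and carry-forward estimates 0.8d. If stopped patients keep a share k of the benefit, the correct value is d(0.8 + 0.2k). For d = 0.50 the estimate is 0.40, against 0.50, 0.45 or 0.40 for k = 1, 0.5 or 0. The error is 0.10, 0.05 or 0.00 SD.

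**Step 3: would imputation do better?** If no stopped patient is reassessed, the effect of the stopping reason cannot be estimated. Imputation from arm and baseline then behaves like a completers' analysis, because baseline predicts nothing in this model. The completers' mean is μ + r·φ(z_p)/(1−p), so at 10%/30% the bias is r(0.1755/0.9 − 0.3477/0.7) = −0.30r at every μ. That is −0.21 for r = 0.7 and −0.30 for r = 1, against −0.12 and −0.17 for carry-forward at μ = 0.

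**Step 4: how wide must a sensitivity analysis be?** Stopped patients lie r·φ(z_p)/[p(1−p)] below completers. At r = 1 this is 0.1755/0.09 = 1.95 SD for 10% stopped and 0.3477/0.21 = 1.66 SD for 30%. At r = 0.7 it is 1.36 and 1.16 SD. Shifts of 0.5 and 1.0 SD would fall short of all four.

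**The case against.** The best defence is that the harm is conditional. The section on discontinuation concerns changing or ending the allocated treatment, not ending follow-up, and the analysis invokes intention-to-treat. Stopped patients may be reassessed, and a rejected exercise test may be repeated. Such follow-up detail can sit in the full protocol. This stands: a reader might infer that stopped patients are not reassessed, but the article neither requires nor excludes it.

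Some stopping is also only loosely tied to outcome. Medication change, infection and free withdrawal are all possible. Both arms receive the full rehabilitation programme, so no average improvement is a strained case. This stands too, and it is why the illustration starts at r = 0.3 and covers improvement up to 0.8 SD, where the bias can change sign. The 15.6% type I error needs every unfavourable assumption at once.

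Finally, the usual replacement, multiple imputation, can be worse than the rule it replaces (step 3). That limits the remedy. It does not rescue carry-forward, since a recalled patient's observed value needs neither.

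**Conclusion.** The point holds in this form: for every named primary and secondary outcome the stated rule is baseline carried forward, and a participant without a usable final value is scored as zero change. That follows from the text alone.

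Size and direction do not. A reader might infer that the rule favours inspiratory training, or that it inflates the false-positive rate in general. The documents support neither. They give no stopping rates by arm and no expected improvement, and equal stopping with no true effect produces no bias. Under the assumed 10%/30% split with nobody reassessed, the effect runs from 0.17 SD against the arm stopped less often to 0.11 SD in its favour. With equal 20% stopping and a true 0.50 SD effect, the estimate is too small by 0 to 0.10 SD.

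This should be changed. Confidence is high in the structural point and only moderate in its practical weight.

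**What to change.** **Evaluated outcomes.** Hold the final assessment at 12 weeks from the start for every participant who can safely undergo it, whatever the number of sessions completed. If a patient is not clinically stable then, postpone within a window set in advance. If exercise testing is not possible, still obtain the scintigraphy (a static acquisition and a primary outcome) and the questionnaire once the patient is stable. Analyse the observed values.

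**Statistical methods.** Do not rely on carry-forward alone. For values still missing, add a sensitivity analysis that gives stopped patients a range of worse changes, varied by arm, and wide enough to include about 2 SD below completers. Use multiple imputation as the main analysis only if enough stopped patients are reassessed to inform it. From arm and baseline alone it assumes that stopped patients resemble completers.

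**Cost.** Wording in two sections. The final assessments are already planned for each participant, and Trial status says recruitment is still open, so later final visits can follow the new rule. The downside is the effort of recalling stopped patients. Some values will stay missing, so the problem is reduced and not removed.
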